#### Usual care (control group)

Usual care is defined as fluid and diuretics administration according to the clinical judgement of the treating ICU physician. The prescribed fluid’s type and amount, as well as the dose of diuretics, will be at the discretion of the ICU physician, guided by clinical and laboratory data, except LUS.

### Data collection and follow-up

Data will be collected on paper-based Case Report Forms and in a secure electronic database for further analysis.

#### Clinical data

Baseline data will include patients’ age, gender, weight and height, reason of ICU admission, data on acute conditions and co-morbidities, on recent immunosuppressive treatments, inflammatory status, infectious status, and severity scores (APACHE II, SOFA, and ISS [only for polytrauma patients]). Except for SOFA severity score, which will be recorded daily, all other severity scores will be calculated once, at ICU admission.

Physiological variables (temperature, heart rate, blood pressure, cardiac rhythm, peripheral blood oxygen saturation, presence of pulmonary crackles or edema), as well as routine laboratory tests (complete blood count, serum electrolytes, urea, and creatinine), will be recorded daily, during ICU stay. Based on case complexity and evolution, all other needed monitoring parameters (e.g. invasive hemodynamic monitoring parameters) and laboratory tests (e.g. arterial-blood gas tests, central venous oxygen saturation, lactate level, inflammatory and infectious biomarkers) will be recorded.

#### Biomarkers

Blood samples will be collected and stored from all study patients, regardless of group allocation, for biomarkers measurement. Serum brain natriuretic peptide (NT-proBNP), interleukin-6 (IL-6), and neutrophil gelatinase-associated lipocalin (NGAL) will be assessed by electro-chemiluminescence “sandwich” immunoassays, using the Roche Elecsys® kit, based on polyclonal antibodies against NT-proBNP, IL-6, and NGAL, respectively. Blood samples will be collected on ICU admission, on the third, fifth, and seventh day of ICU stay, and weekly thereafter, until ICU discharge.

#### Fluid balance and diuretics regimen

Detailed data about daily fluid balance, including route, type and amount of fluid solutions received, and type and volume of fluid losses, as well as data upon diuretic therapy, will be collected daily, during ICU stay.

BLS will be recorded daily in the active group only.

#### Outcome data

Presence and time-course evolution of organ dysfunctions as well as specific therapeutic interventions will be recorded accordantly: hemodynamic support (drug type, dose, and duration of treatment); respiratory support (number of hours on mechanical ventilation); and RRT (type, duration, dose of dialysis, volume of removed fluid, pre and post dialysis BLS in active group only). All complications related to the RRT use will be recorded.

Survival/non-survival at 28 and 90 days since randomization.

### Primary outcome

The main outcome will be death from all causes at 28 days from randomization. This will be assessed by a study team researcher, blinded to patient group assignment, based on hospital recordings or a brief telephone interview with the patient or patients’ legally authorized representative or relative.

### Secondary outcomes

Secondary outcomes will include: presence and time-course evolution of organ dysfunctions during ICU stay; changes in SOFA severity score and biomarkers (NT-proBNP, IL-6, NGAL); ICU length of stay; total hospital length of stay; all-cause mortality at 90 days; resource utilization; and cost–benefit ratio of used fluid solutions (crystalloids/colloids). Secondary outcomes will be assessed based on recorded data during ICU stay, hospital files, and a short telephone interview with the patient or patients’ legally authorized representative to establish 90 days’ survival.

### Strategies to ensure adequate enrolment and protocol compliance

Case Report Forms will be uploaded into a secure database at the trial coordination center in a timely manner. This will allow periodical checks for enrolment rates, data accuracy, and protocol compliance. Whenever necessary, trial coordination center will provide support and feedback to the site investigators.

A safety interim analysis will be conducted after the enrolment of the first 100 patients.

### Statistical analysis

Statistical analysis will be performed using SPSS (SPSS Inc., Chicago, IL, USA) and conducted on an intention-to-treat basis. Frequency distributions will be calculated for all variables and descriptive statistics will be used to define patient’s characteristics in both arms. Study groups will be compared using non-parametric and parametric statistics, according to the types of variables analyzed.

The relative risk of 28-day mortality, with 95% confidence interval, will be assessed in both trial arms. Based on identified mortality-associated variables, we will also perform sensitivity analyses, subgroups analyses, and interactions tests.

Secondary outcomes will be analyzed using univariate analysis and competing-risk methods.

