### Settings

The trial will be conducted in the ICUs of two university hospitals: Saint Spiridon University Hospital and Regional Institute of Oncology Iasi. The ICUs involved in the trial follow the recommendations of the Society of Critical Care Medicine regarding ICU admission and discharge criteria [47], can deliver the same high level of care, and have physicians capable to provide LUS guided fluid therapy. A rapid response team exists in each of these hospitals and ensures on-demand, hospital ward guidance for the management of patients with deteriorating conditions, as well as the evaluation of patients that may benefit from ICU admission.

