### Randomization and blinding

Study patients will be randomly assigned to either LUS guided fluid management or usual care, in a 1:1 ratio, using block randomization. The randomized block design will be created using a computer-based program by a study team member not involved in patient enrollment and treatment. This team member will securely guard the randomized block design at the coordinating center and will provide the allocation sequence each time a new patient is enrolled. Due to study design, patients and ICU physicians cannot be blinded, but the researcher that investigates primary and secondary outcomes will be blinded to patient group assignment.

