### Sample size power calculation

Based on sample size power calculations, for a targeted power of 80% and alpha value of 0.05, the number of patients needed to reveal a significant decrease of 10% in mortality is about 500 (250 in each arm). The mortality benefit estimation is based on a large cohort study of ICU patients, which showed that without any specific intervention, the presence/absence of fluid overload resulted in a mortality rate of 20% and 16.8%, respectively [4].

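### The primary 28-day mortality analysis names no covariates; fixing age, APACHE II, SOFA and centre in advance would add modest precision at almost no cost

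*Protocol article*

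**What the plan says.** - **Endpoint** (Primary outcome): "The main outcome will be death from all causes at 28 days from randomization".
- **Primary analysis** (Statistical analysis): "The relative risk of 28-day mortality, with 95% confidence interval, will be assessed in both trial arms". No covariates are listed. The next sentence adds sensitivity, subgroup and interaction analyses based on variables identified as related to mortality. It does not say which variables, when they are identified, or from what source.
- **Baseline data** (Clinical data): age is listed, and so are "severity scores (APACHE II, SOFA, and ISS [only for polytrauma patients" (the bracket goes on to close). Apart from SOFA, which is recorded daily, the scores are calculated once, at ICU admission.
- **Centres** (Settings): "The trial will be conducted in the ICUs of two university hospitals". Centre is not in the baseline data list but is known for every patient by design.
- **Allocation** (Randomization and blinding): "in a 1:1 ratio, using block randomization". No stratification factor is mentioned.
- **Sample size** (Sample size power calculation): "for a targeted power of 80% and alpha value of 0.05", the number needed to show "a significant decrease of 10% in mortality is about 500 (250 in each arm" patients). The benefit is said to rest on a cohort study in which "the presence/absence of fluid overload resulted in a mortality rate of 20% and 16.8%, respectively".

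**The concern.** Baseline risk in this trial is likely to vary widely. Any one of five criteria is enough for entry: major surgery, surgical patients with major co-morbidities, polytrauma, an APACHE II threshold or a SOFA threshold. One of the two sites is an oncology institute. In such a mix, admission severity should explain part of who dies by day 28. A comparison that ignores it leaves that variation in the treatment contrast.

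Two things are at stake. One is precision: the same 500 patients could give a sharper answer. The other is chance imbalance: if one arm happens to receive sicker patients or more patients from one site, the stated primary estimate has no way to take account of it. An adjusted analysis added later, with covariates not named in advance, would be open to dispute, particularly because treating physicians are not blinded.

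**Working it through.** **Inputs from the article.** 250 per arm; alpha 0.05 (taken as two-sided, since sidedness is not stated); target power 80%; a 10% decrease in mortality (absolute or relative is not stated); cited rates 20% and 16.8%.

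**Input assumed.** The prognostic strength of the baseline variables. The article gives none, so an AUC range of 0.70 to 0.85 is shown (R² about 0.09 to 0.32).

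**Step 1: the plan's own figure.** Per arm, with p̄ the mean of the two rates and d their difference:

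n = [1.960·√(2p̄(1−p̄)) + 0.8416·√(p₁(1−p₁) + p₂(1−p₂))]² / d²

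- 25% vs 15%: [1.960·√0.320 + 0.8416·√0.315]² / 0.10² = 250. This matches the plan, but the article does not state a 25% control rate.
- 20% vs 10%: [1.960·√0.255 + 0.8416·√0.250]² / 0.10² = 199; power at 250 per arm is 88%.
- 20% vs 16.8%: [1.960·√0.3003 + 0.8416·√0.2998]² / 0.032² = 2,301; power at 250 per arm is 15.0%.

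The stated 250 per arm is therefore not reproduced from the rates in the article. Power is adequate for a 10-point drop and far short for the cited 3.2-point difference.

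**Step 2: analytic approximation.** A baseline score explaining a share R² of outcome variance acts like a sample of 250/(1−R²) per arm.

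| Rates | R² = 0 | 0.10 | 0.20 | 0.30 |
|---|---|---|---|---|
| 25% vs 15% | 80.0% | 84.0% | 88.0% | 91.8% |
| 20% vs 16.8% | 15.0% | 16.2% | 17.7% | 19.6% |

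For 80% power at 20% vs 16.8% with 250 per arm, R² would have to be 1 − 250/2,301 = 0.89, well above the assumed range.

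**Step 3: simulation.** 5,000 trials per setting, 250 per arm, one normally distributed baseline score. The two-proportion z test is compared with the Wald test for arm in a logistic model that includes the score. Monte Carlo error is at most about √(0.8·0.2/5,000) = 0.6 points at 80% power. Entries are power in %, unadjusted → adjusted.

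| Rates | AUC 0.70 | AUC 0.76 | AUC 0.80-0.81 | AUC 0.85 |
|---|---|---|---|---|
| 25% vs 15% | 80.2 → 84.1 | 80.4 → 86.1 | 80.7 → 89.2 | 80.3 → 92.0 |
| 20% vs 10% | 88.9 → 90.8 | 89.3 → 92.6 | 88.2 → 93.5 | 88.6 → 95.8 |
| 20% vs 16.8% | 15.4 → 15.6 | 15.2 → 17.0 | 15.6 → 18.2 | 15.7 → 20.0 |

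Separate runs of 4,000 trials used AUC of about 0.72, 0.78 and 0.82:

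- 25% vs 15%: 81 → 85, 79 → 86, 80 → 90.
- 20% vs 10.9%: 80 → 84, 80 → 86, 81 → 89. The 10.9% is not in the article; it is roughly the rate at which 250 per arm gives 80% power from a 20% control rate. A repeat of the weakest setting gave 82 → 84.

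Testing the standardised marginal relative risk instead of the conditional log odds ratio gives essentially the same gain.

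**Step 4: can the model be supported?** At 25% vs 15% the expected deaths are 250·0.25 + 250·0.15 = 100. Arm, age, APACHE II, SOFA and centre make five coefficients, so about 100/5 = 20 deaths per coefficient. At 20% vs 16.8% there would be 50 + 42 = 92 deaths, about 18 per coefficient.

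**The case against.** The strongest reply is that nothing here is wrong. A relative risk by randomised arm is a valid estimate with controlled type I error, and its confidence interval already allows for chance imbalance. The words unadjusted and crude do not appear. A condensed article may leave the covariate list to a full protocol or SAP that is not shown. The simulation is also kind to adjustment, because it uses one perfectly measured, correctly modelled score of assumed strength.

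Most of this stands, and it limits the point to an improvement. It does not remove it. The section does address prognostic variables, and it places them alongside the primary estimate in supplementary analyses. That is a stated choice and more than missing detail.

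A reader might infer more than the documents support:

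- **That adjustment would recover power the trial lacks.** It would not. The gain is useful only where power is already about 80%. At the cited rates power stays below or near 20% even at AUC 0.85.
- **That covariates will be picked after seeing the results.** The wording permits that reading, but says neither when nor from what source they are identified.
- **That allocation was not stratified.** The article is silent on this, and silence in a condensed account does not settle it.
- **That centre is a listed baseline item, or that the surgery is elective.** Neither is stated.

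**Conclusion.** The point holds as a low-cost improvement. As written, the primary analysis is a relative risk with no covariates named, while variables likely to be prognostic are already collected. With a baseline AUC of about 0.72 to 0.82, pre-specified adjustment adds about 4 to 9 points of power where 250 per arm already gives about 80% (25% vs 15%, or 20% vs 10.9%). Single runs at the weakest setting came out as low as about 2 points. Adjustment also gives protection against chance imbalance in severity or centre.

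The size rests on the assumed AUC, a correctly specified model and few missing scores. It does not bear on the gap between the 10% target and the cited 3.2-point difference. That is a sample-size problem and has to be handled as one.

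**What to change.** Before outcomes by arm are examined, write the following into the Statistical analysis section or the SAP:

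1. Primary model: logistic regression for 28-day death with arm, age, admission APACHE II and admission SOFA (all three continuous) and centre.
2. Primary estimate: the standardised (marginal) relative risk, with the risk difference, each with a 95% CI. This keeps the effect measure that the article already names.
3. Supporting analysis: the crude relative risk with 95% CI.
4. A simple, stated rule for imputing missing admission scores that uses baseline data only.
5. Replace the open description of variables to be identified with a named list for the sensitivity, subgroup and interaction analyses.

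No new data and no change to randomisation are needed; the model applies whether or not the blocks were formed within centre. The cost is analysis wording, some programming for the standardised estimate and its interval, and imputation of a few missing scores.

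### Univariate analysis of the changes in SOFA, NT-proBNP, IL-6 and NGAL most naturally leaves out the admission value; adjusting for it would give a more precise comparison at no data cost

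*Protocol article*

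**What the plan says.** Under Secondary outcomes, the protocol article lists "changes in SOFA severity score and biomarkers (NT-proBNP, IL-6, NGAL" among the outcomes. Under Statistical analysis it names the method for all of them in one sentence: "Secondary outcomes will be analyzed using univariate analysis and competing-risk methods". The same section gives the general rule for comparing arms: "Study groups will be compared using non-parametric and parametric statistics, according to the types of variables analyzed".

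The only analyses that go further stand in the paragraph on 28-day mortality: "Based on identified mortality-associated variables, we will also perform sensitivity analyses, subgroups analyses, and interactions tests". No covariate is named for any secondary outcome.

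The admission values exist. For the biomarkers, which are taken in both arms, the Biomarkers section says: "Blood samples will be collected on ICU admission, on the third, fifth, and seventh day of ICU stay, and weekly thereafter, until ICU discharge". SOFA belongs to the baseline data and is then repeated, as the Clinical data section says: "Except for SOFA severity score, which will be recorded daily, all other severity scores will be calculated once, at ICU admission". Under Randomization and blinding, allocation is "in a 1:1 ratio, using block randomization", and no stratification by severity or biomarker level is mentioned.

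**The concern.** Competing-risk methods suit times to an event, such as length of stay, and do not apply to a change in a score or a concentration. For SOFA and the biomarkers that leaves univariate analysis. Read beside the rule on parametric and non-parametric comparison, this is most plausibly a two-group test of change.

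A raw change score subtracts the whole baseline value, so it fixes the baseline slope at 1. If the true slope is below 1, patients with high admission values tend to fall and patients with low values have little room to fall, whatever the treatment. Part of that variation stays in the comparison. The Inclusion criteria admit patients on any one criterion, for example major surgery alone or SOFA ≥ 6, so a wide spread of admission SOFA can be expected.

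At stake is the precision of the outcomes behind the secondary hypothesis on the time course of organ dysfunction. The 28-day mortality endpoint is not touched.

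**Working it through.** **Inputs.** There are 250 patients per arm (Sample size power calculation). That section's design values, "for a targeted power of 80% and alpha value of 0.05", concern 28-day mortality. The protocol states no power or precision for SOFA or the biomarkers, so there is no figure of its own to reproduce here; 80% power at two-sided 0.05 serves only as a reference. The correlation ρ between admission and follow-up values is not given and is assumed over a range. The admission value is taken as unaffected by treatment, since Study design equates randomization with ICU admission.

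**Variance, equal SD σ at both times.** Per patient:

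- change score: 2(1−ρ)σ²
- baseline-adjusted: (1−ρ²)σ²
- ratio, adjusted to change: (1−ρ²) / [2(1−ρ)] = (1+ρ)/2

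**Power.** For an effect that the change score detects with 80% power, adjusted power = Φ(2.802/√ratio − 1.96). The number of patients that matches a change-score analysis of 500 is 500 × ratio.

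| ρ (assumed) | change, σ² units | adjusted, σ² units | ratio | patients matching 500 | adjusted power |
|---|---|---|---|---|---|
| 0.3 | 1.4 | 0.91 | 0.65 | 325 | 93.5% |
| 0.5 | 1.0 | 0.75 | 0.75 | 375 | 89.9% |
| 0.7 | 0.6 | 0.51 | 0.85 | 425 | 86.0% |
| 0.9 | 0.2 | 0.19 | 0.95 | 475 | 82.0% |

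At ρ = 0.5, with all 250 per arm followed, the effect detectable with 80% power is 2.802 × √(2 × 1.0/250) = 0.251 SD by change score and 2.802 × √(2 × 0.75/250) = 0.217 SD after adjustment.

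**Unequal variances.** With SDs σ₀ at admission and σ₁ at follow-up, the change-score variance is σ₀² + σ₁² − 2ρσ₀σ₁ and the adjusted variance is σ₁²(1−ρ²). The difference is (σ₀ − ρσ₁)², which is never negative. The direction therefore does not rest on equal SDs; the size does.

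**Baseline imbalance.** The difference in admission means has SD √(2/250) = 0.089 baseline SDs, so 95% of trials lie within ±0.175. The change-score difference is expected to shift by −(1−ρ) per unit of imbalance. At ρ = 0.5 that is at most about 0.5 × 0.175 = 0.09 SD within that 95% range.

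**Simulation check** (250 per arm, 10,000 runs, no treatment effect). At ρ = 0.3, 0.5 and 0.7 the variance ratios were 0.65, 0.76 and 0.86. The change-score difference moved by −0.71, −0.50 and −0.29 per unit of imbalance, and the adjusted difference by about 0. Both estimates averaged about 0, so neither is biased.

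**The case against.** **The protocol does not literally say unadjusted.** Univariate can also mean one dependent variable, and a univariate linear model can hold covariates. The protocol also gives no reference point or time point for the changes. This stands as a limit on certainty: the concern rests on the most natural reading, not on an explicit exclusion of covariates.

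**Covariates for secondary outcomes are commonly left to an analysis plan, which is not shown.** This stands only in part. The article does not merely leave the method open: it names the outcome as a change and the method as univariate. A plan that followed that sentence in its usual sense would inherit the weakness.

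**The figures may not describe the test that would be run.** Skewed biomarker changes would plausibly get a rank test under the stated rule, and sampling stops at ICU discharge, so fewer than 250 per arm will have later values. This stands. The figures apply to mean-based comparisons with similar SDs. For three of the four outcomes, the gain over a rank test of raw change is not quantified.

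**A reader might infer that the change-score comparison is biased, or that chance imbalance invalidates it.** The protocol does not support that. Allocation is randomized 1:1, the estimate is unbiased on average, and with 250 per arm the sensitivity to imbalance is modest.

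**Conclusion.** The concern holds as a matter of efficiency. On the natural reading of the Statistical analysis section, the arms would be compared on change in SOFA and the biomarkers without the admission value. That comparison is valid under randomization, but less precise than the data allow and sensitive to the imbalance that actually arises.

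The size depends on ρ, which is assumed. The variance would fall by 35% at ρ = 0.3 and by 25% at 0.5, but by only 5% at 0.9, where the reference power rises by about 2 points. These figures assume mean-based comparisons, equal variances and, for the detectable effects, complete follow-up.

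The point concerns secondary outcomes for which no power is claimed. It is an improvement of modest importance and does not show that the planned comparison would mislead.

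**What to change.** In the Statistical analysis section, give SOFA and the three biomarkers their own method:

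- Compare arms on the post-admission values at the scheduled times: SOFA daily, biomarkers on days 3, 5 and 7. State whether the later weekly samples enter the model.
- Use a linear or repeated-measures model with arm, time, arm by time and the admission value of the same measure.
- Analyse NT-proBNP, IL-6 and NGAL on the log scale.
- Report the adjusted difference, or the ratio of geometric means for the biomarkers, with its 95% confidence interval. Keep raw change as description only.

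If adjustment is already intended, the sentence should say so.

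The cost is a short paragraph before database lock and a few lines of code in the stated software, SPSS. No new data, patients or staff are needed. Results would be read as baseline-adjusted differences instead of raw changes. How to handle values missing after death or ICU discharge is a separate matter that this change does not settle.

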### Sample size power calculation

Based on sample size power calculations, for a targeted power of 80% and alpha value of 0.05, the number of patients needed to reveal a significant decrease of 10% in mortality is about 500 (250 in each arm). The mortality benefit estimation is based on a large cohort study of ICU patients, which showed that without any specific intervention, the presence/absence of fluid overload resulted in a mortality rate of 20% and 16.8%, respectively [4].

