**Methods:**

LUS Guided Fluid Management Protocol for the Critically Ill Patient is a prospective, multi-centre, randomized controlled trial. Five hundred ICU patients will be randomly assigned in a 1:1 ratio, to protocolized LUS-based fluid management or usual care. The trial intervention will start on ICU admission and will consist in daily assessment of BLS and triggered evacuation of excessive fluids with loop diuretics (Furosemide) when BLS ≥ 15. If rebalancing volume status with diuretics fails, forced evacuation by ultrafiltration will be used. The main endpoint is death from all causes at 28 days from randomization. The secondary outcomes are presence and time-course evolution of organ dysfunctions, ICU- and hospital length of stay, all-cause mortality at 90 days, and health economics data.

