### Study interventions

#### LUS guided fluid management (active group)

LUS guided fluid management is based on BLS assessment using LUS, within the first 24 h of ICU admission, and daily thereafter, until ICU discharge, or for up to 28 days after randomization, whichever comes first.

After the initial LUS examination, the follow-up LUS will be performed daily, in the morning, at set times, between 9 am and 11 am. The rationale for this approach is that all ICU patients will have daily, in the morning, a full clinical examination and a complete set of laboratory tests, providing evaluation of fluid status. In this way, all collected data may be further correlated with LUS findings.

LUS examinations will be performed at bedside, with the patient in a supine position, using the 28 zone technique and the GE LOGIQ V2® ultrasound system with the GE 3Sc-RS Cardiac Sector Probe® (1.5–4.0 MHz frequency). The focus of the image will be set at the level of the pleural line and the depth of penetration at around 4–8 cm. The image will be optimized by regulating the gain. The lungs will be scanned, from the second to the fourth intercostal space on the left side, and from the second to the fifth intercostal space on the right side, at parasternal, mid-clavicular, anterior-axillary, and mid-axillary lines. B-lines will be recorded in each intercostal space (28 sites of examination). The sum of all B-lines will produce a score, BLS, reflecting the extent of EVLW accumulation.

The ICU physician may recommend fluid therapy or vasoactive drugs with types and amounts at his/her choice. However, when signs of moderate/severe pulmonary congestion are seen on LUS exam (BLS ≥ 15), a negative 24-h fluid balance (250–1000 mL) will be intended according to clinical judgement.

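### The 10% mortality target is attributed to a cohort contrast of 3.2 points (20% vs 16.8%), for which 500 patients give about 15% power, not 80%

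*Protocol article*

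**What the plan says.** The Sample size power calculation section of the protocol article sets the design values "for a targeted power of 80% and alpha value of 0.05" and concludes that "the number of patients needed to reveal a significant decrease of 10% in mortality is about 500 (250 in each arm"). It does not say whether the 10% is absolute or relative, and it attaches no control-arm rate to it.

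The next sentence gives the source of the effect: "The mortality benefit estimation is based on a large cohort study of ICU patients". In that cohort, with no specific intervention, "the presence/absence of fluid overload resulted in a mortality rate of 20% and 16.8%, respectively". These are the only mortality rates in the section.

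The endpoint being powered is binary: "The main outcome will be death from all causes at 28 days from randomization" (Primary outcome). Allocation is 1:1 (abstract, Methods). The Statistical analysis section plans an intention-to-treat analysis and a relative risk with a 95% confidence interval.

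**The concern.** The section gives a power, an effect and a source for the effect, and these do not fit together. A reader would conclude that the trial has 80% power for the benefit that the cohort suggests. The cohort's difference is about a third of an absolute 10 points (3.2 / 10 = 0.32).

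The primary endpoint is at stake. If the true benefit is of the size the rationale cites, a non-significant result is by far the most likely outcome. A reader relying on the stated 80% could then take it as evidence that ultrasound guidance does not reduce mortality.

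**Working it through.** **Inputs.** From the Sample size power calculation section: power 80%, alpha 0.05, 250 per arm, cited rates 20% and 16.8%. Sidedness is not stated, so two-sided is assumed and one-sided is also shown.

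**Formulas** (two proportions, pooled variance under the null, 1:1), with p̄ = (p1 + p2)/2 and d = p1 − p2:

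- n per arm = [1.960·√(2p̄(1−p̄)) + 0.842·√(p1(1−p1) + p2(1−p2))]² / d²
- power = Φ[(d − 1.960·SE0)/SE1], where SE0 = √(2p̄(1−p̄)/n) and SE1 = √((p1(1−p1) + p2(1−p2))/n)

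**Step 1: the plan's own figure.** An absolute 10-point fall gives 250 per arm for 25% vs 15%: [1.960 × 0.5657 + 0.842 × 0.5612]² / 0.10² ≈ 250, power 80.0%. Neither rate is in the article, and this is not the only fit:

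- Two-sided without continuity correction, control rates of about 24.2% to 25.7% give roughly 500 in total.
- With continuity correction the range is about 22.3% to 23.6%.
- One-sided without correction it is about 32% to 35%.
- A relative 10% fall gives 500 only at a control rate of about 89% to 90%, so an absolute reading is the only plausible one.

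**Step 2: 10% taken from the cited 20%.**

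- Absolute, 20% vs 10%: [1.960 × 0.5050 + 0.842 × 0.5000]² / 0.10² ≈ 199 per arm (219 with continuity correction). Power at 250 per arm is 88%.
- Relative, 20% vs 18%: [1.960 × 0.5548 + 0.842 × 0.5546]² / 0.02² ≈ 6,039 per arm. Power at 250 per arm is 8.2%, or 8.8% counting both tails.

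Neither gives 250.

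**Step 3: the cited contrast.**

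- Size: 20% − 16.8% = 3.2 points; 3.2/20 = 16% relative.
- n = [1.960 × 0.5480 + 0.842 × 0.5475]² / 0.032² ≈ 2,301 per arm, 4,602 in total.
- Power at 250 per arm: SE0 = 0.03466 and SE1 = 0.03463; (0.032 − 1.960 × 0.03466)/0.03463 = −1.04; Φ(−1.04) ≈ 15.0%. Exact enumeration of the chi-square test gives 15.1%.
- One-sided: power 23.5%, and 1,812 per arm for 80%.

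**Step 4: what 250 per arm can detect from 20%.** Solving the power formula for 80% gives a fall of about 9.0 points, to about 11.0%. That is 9.0/3.2 ≈ 2.8 times the cited difference.

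| Control vs active | n per arm for 80% | Power at 250 per arm |
|---|---|---|
| 25% vs 15% (not stated) | 250 | 80% |
| 20% vs 10% | 199 | 88% |
| 20% vs 18% | 6,039 | 8–9% |
| 20% vs 16.8% (cited) | 2,301 | 15% |

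**The case against.** **The figure of 500 is not an arithmetic error.** This stands. It is right for an absolute 10-point fall from about 25%, and more than enough for a fall from 20% to 10%. A reader might infer that the sample size is simply miscalculated. The article does not show that; it shows a target whose stated source does not support it.

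**A condensed article may leave the control rate, scale and sidedness to the full protocol.** This also stands, and their absence alone would be no finding. The cited cohort may contain other figures nearer 10 points, but the article does not mention any. What remains is the mismatch between two adjacent sentences, which does not depend on anything missing.

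**25% vs 15% is only a reconstruction.** Correct. With continuity correction 23% vs 13% also gives 250 per arm, and 398 inflated for 20% dropout gives 398/0.8 ≈ 498. None of these is documented, so none can be presented as the sponsor's input.

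**The cohort contrast is not an estimate of the treatment effect.** True, and it works in both directions. The trial enrols patients whether or not they are congested, and the active arm aims for a negative fluid balance only "when signs of moderate/severe pulmonary congestion are seen on LUS exam". The intention-to-treat effect may therefore be smaller than 3.2 points. A reader might go on to put a figure on this dilution, but the article gives no proportion of patients expected to reach the threshold, and it does not equate the cohort's fluid overload with BLS ≥ 15. Patients selected by severity scores may also have a control rate other than 20%.

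**Interval estimation is already planned.** It is, so interpreting the result from the interval needs no new analysis.

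**Conclusion.** The point holds as a mismatch between the power statement and its stated basis. For the cited 20% vs 16.8%, 250 per arm gives about 15% power at two-sided 0.05 (23.5% one-sided), and 80% would need about 2,301 per arm. No 10% reading from the cited 20% reproduces 250 per arm. The 80% applies to an absolute fall of about 9 to 10 points from a control rate of 20% to 25%, and the article gives no evidence for a fall of that size.

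The figures assume an uncorrected two-proportion test with no dropout; the exact test agrees, and sidedness does not change the conclusion.

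A reader might also infer that any significant result would be a large overestimate. That follows only if the true effect is near 3.2 points. Significance then needs an observed difference of about 1.960 × 0.0347 = 6.8 points, roughly twice the true one. The article does not establish what the true effect is, so the inference stays conditional.

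**What to change.** Revise the Sample size power calculation section as follows.

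1. State the control-arm 28-day mortality actually assumed and its source, that the 10% is an absolute reduction, and whether alpha is two-sided. The sponsor should supply the rate that was used. Writing in 25% vs 15% because it fits would replace one undocumented basis with another.
2. Report that, from the cited 20%, 250 per arm has 80% power (two-sided 0.05) for a reduction of about 9.0 points or more, and about 15% power for the cited 3.2-point contrast.
3. Stop presenting the 20%/16.8% cohort as the basis of a 10-point benefit, unless data supporting 10 points are cited. It can remain as background on the association of fluid overload with mortality.
4. State that a non-significant result will be interpreted from the planned 95% confidence interval and not as evidence of no benefit.

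The cost is wording only: no extra patients and no access to outcome data. Power itself does not change; the stated position becomes less favourable, and a null result is less likely to be misread.
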